**Fig. 3 Fig3:**
[figure not shown]
Diagram depicting scanner task

##### Regulation-of-craving task data preprocessing

The fMRI images will be realigned to the third slice collected in each scanning session to correct for motion. The images will be spatially smoothed with a 4-mm full width at half maximum (FWHM) Gaussian blur. Timepoints during which participants move more than 0.3 mm within a TR will be censored. Functional and anatomic images obtained within each session will be aligned and normalized to Talairach and Tournoux’s [35] stereotaxic atlas. Regressors representing the experimental conditions of interest (i.e., positive smoke, negative smoke, positive food, and negative food) will be modeled with a block response function and entered into the multiple-regression analysis using a random-effects model. Motion parameters will be included as nuisance regressors.

The primary contrast of interest will be negative smoke minus positive smoke, which represents an analog of the exertion of cognitive control minus general brain activation engendered by attending to smoking cues. The primary outcome analysis will focus on the a priori ROI, the dlPFC. In addition, an exploratory whole-brain analysis will be used to identify regions outside the dlPFC cognitive control network that may change with practice (e.g., the insula). The dlPFC ROI has been selected based on previous studies [5, 23, 24, 36]. The dlPFC will be defined using anatomical masks for the dlPFC based on the superior frontal gyrus and the middle frontal gyrus regions identified by AFNI’s whereami function. Multiple comparisons will be corrected using a familywise approach in which clusters will be considered significant at *p*_voxelwise_ < .01 and *p*_corrected_ < .05 within the dlPFC for the ROI analysis and within the whole-brain for the exploratory whole-brain analysis. The minimum cluster size will be determined using AFNI’s 3dClustSim function. The spatial autocorrelation function (acf) option was used in AFNI’s 3dFWHMx to estimate intrinsic smoothness and 3dClustSim to estimate the probability of false positives [37, 38]. The mean percentage signal change from dlPFC clusters that pass cluster thresholding will be used as the primary outcome data to test the hypothesis described in aim 1.

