#### Analysis plan

The planned data analyses are built around three specific aims. The first aim is to compare changes in brain activation in cognitive control regions as a result of cognitive control practice. The second aim is to determine the effect of adherence to the practice regimen on changes in brain activation in cognitive control regions. The third aim is to explore the effects of individual differences (e.g., level of tobacco dependence, motivation, and sex) on changes in brain activation in cognitive control regions.

##### Aim 1

Our primary aim is to identify the impact of practicing delaying the first cigarette of the day compared to not practicing on functional brain activation changes in cognitive control regions. The percentage signal change when comparing the negative smoke condition to the positive smoke condition will be computed for our a priori cognitive control region of interest (ROI) (i.e., dlPFC) for each subject at each time point and entered into a two-way mixed-effects ANOVA model using the group (practice, no practice) × time (pre, post) interaction. We hypothesize that practice vs. no practice will lead to greater pre-to-post brain activation *increases* in the cognitive control network.

##### Aim 2

We will also identify the impact of *adherence* to practicing delaying cigarettes on functional brain activation changes in the cognitive control networks in response to smoking cues. Using only participants from the practice group, we will calculate Pearson correlations between differences in brain activation from the negative smoke and positive smoke conditions and amount of practice completed. Brain activation will be computed as percentage signal change from pre- to post-treatment in response to smoking cues in the a priori dlPFC ROI. Practice will be quantified as the proportion of time delayed from their usual first cigarette of the day to their second cigarette of the day and subjectively measured by participants’ perceived difficulty in delaying the first cigarette of the day. We hypothesize that greater levels of practice will show greater brain activation increases in the cognitive control network in response to negative smoke compared to positive smoke conditions from pre- to post-intervention.

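### The Aim 1 primary outcome is defined in two ways; the cluster-based version does not name its selecting map and has no value if no cluster passes

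*Protocol article*

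**What the plan says.** **Analysis plan, Aim 1.** Percentage signal change for negative against positive smoke "will be computed for our a priori cognitive control region of interest (ROI) (i.e., dlPFC) for each subject at each time point" and then goes into a "two-way mixed-effects ANOVA model using the group (practice, no practice) × time (pre, post) interaction". Aim 2 also refers to the a priori dlPFC region.

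**Regulation-of-craving task data preprocessing.** This section first agrees with Aim 1: "The primary outcome analysis will focus on the a priori ROI, the dlPFC". The region is anatomical and so independent of the trial's data: "The dlPFC will be defined using anatomical masks for the dlPFC based on the superior frontal gyrus and the middle frontal gyrus regions". It names one contrast: "The primary contrast of interest will be negative smoke minus positive smoke". It then sets a cluster rule, "Multiple comparisons will be corrected using a familywise approach in which clusters will be considered significant at" voxelwise p < .01 and corrected p < .05, applied within the dlPFC for the region analysis and across the brain for the exploratory analysis. Its last sentence changes the endpoint: "The mean percentage signal change from dlPFC clusters that pass cluster thresholding will be used as the primary outcome data", to be used for the Aim 1 hypothesis.

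**Power and sample size.** The calculation is a two-sided two-sample t-test at 0.05/2 = 0.025 with 40 per group. For the dlPFC it takes d = 0.70 and states 79% power.

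**The concern.** The mean over a whole anatomical mask and the mean over whichever parts of it pass a threshold are different quantities. The second depends on the trial's own data, so how it behaves depends on which map does the selecting, and the article does not say.

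If voxels are kept because they show a group × time effect and are then tested for that effect, the second test adds nothing and the estimated effect is too large. The article hopes to establish a biomarker and to use such effects in deciding which interventions to scale up, so the size of the estimate matters as well as the p-value.

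An outcome that exists only when some cluster passes also leaves the planned ANOVA without data in the remaining cases.

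**Working it through.** **1. The plan's own figure.** Inputs from Power and sample size: n = 40 per group, d = 0.0991/0.1415 = 0.70, two-sided alpha 0.025. Noncentrality is d × √(n/2) = 0.70 × √20 = 3.13 on 78 df. Power from the noncentral t is 79.9%, against 79% stated. For d = 1.08 (vmPFC) it is 99.4%, against > 99% stated. The figures reproduce. They describe one two-sample test and make no allowance for a selection step.

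**2. Selection on the group × time map.** With two time points the interaction test equals a two-sample t-test on change.
- Two-sided voxelwise p < .01 requires |t(78)| > 2.64.
- In units of d: 2.64 × √(2/40) = 0.59. Every retained voxel has an observed |d| of at least 0.59.
- Within a cluster of one sign, the mean difference is the average of the voxel differences, and the SD of the cluster mean is at most the average voxel SD. The cluster mean therefore also has |d| ≥ 0.59 and p < .01, which is already below 0.025.

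This floor does not depend on mask or smoothness. The size of the inflation does, so it was simulated with no true group × time effect, 40 per arm and an extent threshold set at the 95th percentile of the largest null cluster. Mask and smoothness are assumptions, not figures from the article.

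| Null simulation | Runs with a passing cluster | Follow-up test significant | Observed \|d\| (truth 0) |
|---|---|---|---|
| 18×18×10 voxels, 8 mm effective smoothness, 800 runs | 23 (2.9%) | 23 of 23 at .05 (largest p 0.000014) | mean 1.16 |
| 20×20×14 voxels, Gaussian kernel SD 1.2 voxels, 300 runs | 13 (4.3%) | 13 of 13 at .025 | median 1.17 |

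The overall false-positive rate is the share of runs with a passing cluster, because the follow-up never fails. It stays near .05, since the cluster step is itself familywise corrected. It is not held at 0.025.

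**3. Selection on negative minus positive smoke, pooled over arms and scans.** Let M be a participant's mean of the two scans and D the change between them. The covariance of the pooled mean of M with the arm difference in D is (c₁ − c₂)/80, where c₁ and c₂ are the within-arm covariances of M and D. It is zero when the arms share a covariance structure, as they do under the null. In the 300-run simulation, with an assumed task effect of 0.5 SD in part of the mask, all 300 runs had a passing cluster. The Aim 1 test rejected in 4.3% at .05 and 2.3% at .025, so there is no circularity.

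**4. No passing cluster.** On the group × time map under the null, no cluster passed in 777 of 800 runs (97.1%) and 287 of 300 (95.7%). Under the planning effect, a single voxel with true d = 0.70 passes p < .01 with probability 68.7%. That is illustrative only, because cluster passage also depends on extent.

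**5. The full anatomical mask.** In the 300 null runs the whole-mask mean always existed and rejected in 4.0% at .05 and 2.0% at .025.

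**The case against.** The strongest reply is that circularity is not in the text. The only contrast named is negative minus positive smoke, and finding dlPFC clusters on that contrast and then testing group × time in them is a natural and valid procedure. This stands. A reader might infer from the final sentence that the primary test is circular and cannot fail, but the article does not support that as a flat statement. The pointer the other way is that the same thresholds are set for a whole-brain search for regions whose activity changes with practice. That suggests a group × time map without stating one, and it describes the exploratory analysis.

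A reader might also infer an inflated false-positive rate. Even in the circular case it stays near .05; the shortfall is only against the 0.025 of the sample-size section.

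On missing outcomes, it can be said that no passing cluster on a group × time map is simply a negative corrected result, and that an empty map is less likely for the pooled task contrast, since the Design justification chose the task for robust dlPFC activation. Both points are fair. The first still leaves the specified ANOVA without data or an effect estimate; the second lowers the probability without giving a fallback.

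It could be argued that the selecting map and the fallback belong in a full protocol or SAP not shown here. That may be so, but the conflict between the two stated outcomes is in this document.

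Nor can it be said that d = 0.70 was derived for one outcome and not the other: the article does not say how the pilot dlPFC signal was extracted.

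**Conclusion.** The point holds in a limited form. The article states two different primary outcomes for Aim 1, and the cluster-based one has no value when no cluster passes; neither statement needs any assumption.

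Circularity is conditional on the unstated map. If that map is group × time, a same-sign cluster has observed |d| of at least 0.59 by construction with 40 analysed per arm, the second p-value carries no evidence, and the effect estimate is inflated, to about 1.2 against 0 in null simulations that rest on an assumed mask and smoothness. If the map is the pooled task contrast, none of this applies. Because validity turns on a choice the article leaves open, the choice should be fixed before any group comparison.

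**What to change.** Replace the last sentence of the preprocessing section so that it says: the primary outcome is the mean percentage signal change, negative smoke minus positive smoke, over all voxels of the pre-defined anatomical dlPFC mask, extracted for every participant and scan and tested once under Aim 1. Label the within-dlPFC cluster analysis of group × time as exploratory localisation.

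If a functional sub-mask is preferred, define it from a contrast independent of group × time, for example negative minus positive smoke pooled over arms and scans. Fix it before any group comparison, say how several clusters are combined, and name the full mask as the fallback if no cluster passes.

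The cost is wording only. The sample size does not change: the stated power calculation describes a fixed-region test of this kind (79.9% at d = 0.70 and alpha 0.025). The downside is that a mean over the superior and middle frontal gyri may dilute a focal effect. The size of that dilution cannot be derived from the article; the exploratory cluster map could still show such an effect.

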##### Resting state scan

Prior to completing the regulation-of-craving task, approximately 10 min of resting state data will be acquired while participants are instructed to keep their eyes open and focused on a fixation cross at the center of the screen. Heart rate and respiration rate will be collected using Biopac (BIOPAC MP150 Data Acquisition). This scan will be used in exploratory analyses to examine changes in resting state connectivity between cognitive control regions and the rest of the brain following the intervention*.*

##### Resting state data preprocessing

Freesurfer will be used to segment gray matter, white matter, and cerebral spinal fluid. In addition, respiration and heart rate will be processed using AFNI’s RetroTS. Preprocessing analysis scripts will be built using afni_restproc.py [39]. Preprocessing will include removing the first four volumes, removing any transient signal, slice time correction, and co-registering all functional data to the first volume. Nuisance variables will be measured [i.e., six motion parameters (three translations and three rotations), average ventricle signal and average local white matter signal (15-mm spherical neighborhood, 3dLocalstat)] and removed from the signal time course using multiple regression. The residual time course images will then be smoothed with a 6-mm FWHM Gaussian kernel, resampled to a 2 × 2 × 2 mm grid, and spatially normalized to Talairach stereotaxic space. In addition to controlling for six motion parameters, further motion correction procedures (i.e., scrubbing) will be used to reduce the possibility of type I errors related to motion [40, 41]. Time points with greater than 0.3-mm motion will be censored.

#### Self-report assessments

##### Smoking characteristics

The Fagerström Test for Nicotine Dependence [42] will assess nicotine dependence. Items from the COMMIT Smoking Prevalence Survey [43] will assess smoking history such as tobacco use (cigarettes per day (CPD) and other tobacco use), age when first smoked, and quitting/relapse history. Because neural responses may be influenced by motivation to quit, we will assess this by asking: “How motivated are you to quit smoking?” on a scale from 0 to 10.

##### Individual differences in personality, smoking attitudes, and mood

Autonomous regulation for smoking cessation will be assessed using the Treatment Self-Regulation Questionnaire [44], an established measure of internalized motivation for behavior change. Self-report impulsivity will be measured with the Barratt Impulsivity Scale (BIS-11) [45] and the UPPS-P Impulsive Behavior Scale [46]. Sensitivity to reward will be measured with the Sensitivity to Punishment/Sensitivity to Reward Questionnaire (SPSRQ) [47]. Items from the multidimensional Brief Wisconsin Inventory of Smoking Dependence Motives [48] will assess primary and secondary dependence motives. The Patient Health Questionnaire-9 (PHQ-9) [49], Generalized Anxiety Disorder-7 scale (GAD-7) [50], and Attention-Deficit/Hyperactivity Disorder (ADHD) Symptoms scale (from the PhenX Toolkit [51]) will assess depression, anxiety, and ADHD symptoms, respectively.

##### Other tobacco and substance use

Participants will answer questions on cannabis addiction, which focuses on the diagnostic criteria for cannabis use disorder. To create this measure, we adapted questions from the Yale Food Addiction Scale [52], which assesses multiple aspects of addiction, such as tolerance, frequency of use, and preoccupation. Other tobacco and substance use will be characterized using the following instruments from the PhenX Toolkit [51]: Use of Tobacco Products, Substances: 30-day Frequency, Substances: Lifetime Use.

#### Behavioral measures

Measures of the demand for cigarettes, executive function/inhibitory control, risk-taking, and impulsive choice will be administered outside of the scanner to test if practice leads to behavioral changes.

##### Demand for cigarettes

A cigarette purchase task [53, 54] will be used to measure the demand for cigarettes. In this task, participants are asked how many cigarettes they would smoke in a day across a wide range of hypothetical per-cigarette prices ($0.01 to $35). The resulting data will be modeled to yield a number of economic indicators related to demand including elasticity, intensity, breakpoint, and maximum expenditure.

##### Executive function and inhibitory control

A Stroop task and a go/no-go task will be used as measures of executive function/inhibitory control. In the Stroop task [55], participants are asked to press keyboard buttons corresponding to the font color of neutral words (e.g., “when” and “and”) and color words (e.g., “blue” and “red”) presented on-screen using the Psychology Experiment Building Language (PEBL) [56]. In some trials (incongruent trials), the color words are presented in a mismatching font color (e.g., the word “yellow” in a green font). In these cases, participants must ignore the semantic content of the word to get the correct answer. Errors and the response times in these trials (compared to the congruent trials) will be used as the primary variables.

In the go/no-go task [57], participants consecutively see individual letters on a computer monitor. This test was developed using E-Prime 3.0 (Psychology Software Tools, Inc., Sharpsburg, PA, USA). Participants are asked to press a button if and only if a certain sequence of letters occurs (e.g., “S” followed by “T”). These are considered go trials. When “S” is followed by any other letter, it is considered a no-go trial. Several measures will be computed including the percentage of correct go responses, mean reaction time of go responses, percentage of false alarms (overall and just on no-go trials), and impulsivity and inattention scores as defined by Overtoom et al. [58].

##### Risk-taking

The PEBL version of the balloon analog risk task [59, 60] will be used to assess risk-taking. Participants will be asked to press a button that pumps up an on-screen balloon. Every pump is rewarded with a small amount of virtual money but carries the risk of bursting the balloon. Participants may choose to bank the money earned for a balloon at any time, thus ending the trial. Popping the balloon resets the money counter back to zero and starts a new trial. The number of popped balloons and the total banked money on non-popped trials will be used as primary measures.

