##### Aim 3 (exploratory)

Finally, we will examine the association between practice-related brain activation changes in the cognitive control and reward networks and individual differences (e.g., dependence, motivation, gender, self-report measures of impulsivity, and behavioral measures of cognitive control). We will perform Pearson correlation analyses to examine the relationship between dlPFC brain activation changes (i.e., the percentage signal change in response to negative smoke compared to positive smoke conditions from pre- to post-treatment) and motivation to quit smoking, nicotine dependence, personality and psychological variables, and cognitive performance. In addition, we will use *t*-tests to examine gender differences in brain activation changes. Finally, we will use multiple regression to explore the effects of gender, marijuana use, motivation to quit smoking, dependence, self-report measures of impulsivity, and behavioral measures of executive function, decision-making, inhibition, and demand on changes in cognitive control.

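### Total banked money in the balloon task has no fixed direction as a risk-taking measure when analysed alone

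*Protocol article*

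**What the plan says.** The Risk-taking section of the protocol article sets out the rules of the balloon task: "Every pump is rewarded with a small amount of virtual money but carries the risk of bursting the balloon". It adds: "Popping the balloon resets the money counter back to zero and starts a new trial". Participants may bank at any time, which ends the trial. The section then fixes the scoring: "The number of popped balloons and the total banked money on non-popped trials will be used as primary measures". It gives no burst probability, number of balloons, money per pump or expected pumping range.

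Two other places bear on how the scores will be used.

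- The opening of Behavioral measures says that these tasks, risk-taking among them, "will be administered outside of the scanner to test if practice leads to behavioral changes".
- Aim 3, which is labelled exploratory, says: "We will perform Pearson correlation analyses to examine the relationship between dlPFC brain activation changes", with cognitive performance among the variables to be correlated. It also plans a multiple regression that includes "behavioral measures of executive function, decision-making, inhibition, and demand on changes in cognitive control". Aim 3 names neither risk-taking nor the balloon task.

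**The concern.** A score for risk-taking should move one way as risk-taking increases. Total banked money does not. It is the number of pumps multiplied by the share of balloons that survive them, and these two factors pull in opposite directions. If practice raised the mean total, that could mean more risk-taking among participants who pump too little to maximise earnings, or less risk-taking among those who pump too much. A linear coefficient relating the total to dlPFC change has the same ambiguity.

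The two named measures can also part company. Below the earnings optimum, more pumping raises both the pops and the money. Above it, more pumping raises the pops and lowers the money. The article calls both measures primary for the task and does not say how to read them when they disagree, which leaves that choice until after the results are seen.

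**Working it through.** The article states no figure for this task, so there is no figure to reproduce. The check has three steps.

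**1. From the task rules alone.** A participant who never pumps banks 0. A participant who pumps until nearly every balloon bursts banks close to 0. Anyone in between banks more. The total must therefore rise and then fall. This needs only the assumption that continued pumping almost always ends in a burst.

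**2. Expected money under assumed schedules.** Let k be the intended number of pumps per balloon, with one unit of money per pump (assumed). Expected money per balloon is k × P(survive k pumps).

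*Burst point uniform with maximum M* (assumed): k(1 − k/M). With M = 128:
- k = 32: 32 × 0.75 = 24 units, 25% of balloons popped
- k = 64: 64 × 0.50 = 32 units, 50% popped (the maximum)
- k = 96: 96 × 0.25 = 24 units, 75% popped

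A threefold difference in pumping gives the same money. For M = 8, 32 and 64 the peak is again at M/2, with equal money at M/4 and 3M/4.

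*Constant burst risk h per pump* (assumed): k(1 − h)^k. With h = 1/32, the result is 9.6 units at 16 pumps, 11.6 at 32 and 8.4 at 64. For h = 0.01, 0.02, 0.05 and 0.10 the peak is at 99, 49, 19 and 9 pumps, with 61% to 63% of balloons popped at the peak.

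**3. What a linear analysis would see.** A simulation assumed 30 balloons, M = 128 and 200,000 participants per scenario. Each participant had one intended k, drawn uniformly over the stated range of k/M. Pops were binomial(30, k/M), and money was (30 − pops) × k. The table gives the Pearson correlation of k with each measure, and the R² for predicting k from pops and total money together.

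| Range of k/M | Total money | Popped balloons | R², both together | Money per non-popped balloon |
|---|---|---|---|---|
| 0.05–0.50 | 0.89 | 0.86 | 0.97 | 1.000 |
| 0.10–0.60 | 0.75 | 0.87 | 0.96 | 1.000 |
| 0.05–0.70 | 0.69 | 0.92 | 0.95 | 1.000 |
| 0.20–0.80 | 0.00 | 0.90 | 0.92 | 0.999 |
| 0.05–0.95 | 0.00 | 0.96 | 0.94 | 0.955 |
| 0.50–0.95 | −0.72 | 0.86 | 0.85 | 0.714 |

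The zeros follow from symmetry: k(1 − k/M) is symmetric about M/2, and so are those two ranges.

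The last column equals 1 by construction wherever at least one balloon survives, because money ÷ (30 − pops) is then exactly k. It falls below 1 only because simulated participants who popped all 30 balloons were scored 0. At k/M = 0.95 the chance of that is 0.95^30 ≈ 0.21.

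**The case against.** A reader might go further and infer that the planned analyses cannot tell cautious participants from reckless ones. The article does not support that. Popped balloons is named in the same sentence, rises with risk-taking in every scenario, and separates the two kinds of participant (25% against 75% popped in the example above). Taken together, the two named measures recover most of the information on pumping. With a fixed number of balloons and constant pay per pump, they even determine the index proposed below: total money ÷ (balloons − pops) ÷ pay per pump. This objection stands. It limits the point to the total analysed alone, which is how a Pearson correlation or a comparison of means would treat it. The article describes no joint reading for this task.

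The link to Aim 3 is also an inference. Cognitive performance and decision-making plausibly include this task, but Aim 3 does not say so. If the total were meant as a measure of how well participants performed, more would simply be better. That is fair as far as it goes, but the article introduces the task as a measure of risk-taking. Nor does Pearson correlation require a monotone score. The coefficient is valid as a measure of linear association; the difficulty is what it says about risk-taking.

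Finally, the loss is not certain. If all participants stay below the optimum, the total tracks pumping well (0.89). The article gives nothing that settles which case applies.

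It can also be said that a condensed article leaves scoring detail to the full protocol. That would excuse silence, but here the article does name the measure and calls it primary for the task.

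**Conclusion.** The point holds in a limited form. Total banked money is an ambiguous, non-monotone measure of risk-taking, and this follows from the article's own task rules. A mean change in it, or a linear coefficient if Aim 3 covers this task, has no fixed direction when the total is analysed alone. The size cannot be fixed from the article: under the assumed uniform schedule and 30 balloons, the correlation with intended pumping ranges from 0.89 to −0.72.

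The consequence is small. Primary here means primary for this one task. The trial's primary outcome is dlPFC signal change, and neither that test nor the sample size depends on the balloon task. Only behavioral and exploratory results are affected, and popped balloons remains a usable measure for them.

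**What to change.** In the Risk-taking section, name the mean number of pumps per non-popped balloon as the risk-taking measure alongside the number of popped balloons. If pay per pump is constant, mean money per non-popped balloon is equivalent. Report total banked money descriptively, as task earnings. State also how a participant who pops every balloon is handled, since the mean is then undefined. The last row of the table shows that scoring such participants as zero weakens the index, which is one reason to keep popped balloons beside it.

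The cost is a sentence or two of wording. Pump counts underlie the money already earned in the task, so no new data are needed. Making the change before analysis gives any behavioral-change comparison or Aim 3 analysis of this task a readable direction.
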